# *Banha-sasim-tang *as an herbal formula for the treatment of functional dyspepsia: a randomized, double-blind, placebo-controlled, two-center trial

**DOI:** 10.1186/1745-6215-11-83

**Published:** 2010-07-30

## Abstract

**Background:**

Functional dyspepsia (FD) is characterized by a high prevalence rate and no standard conventional treatments. Alternative therapies, such as herbal formulas, are widely used to treat FD. However, there are inadequate evidences regarding the safety and efficacy of these formulas. Moreover, the mechanisms by which herbal formulas act in the gastrointestinal tract are controversial. In traditional Korean medicine, *Banha-sasim-tang *has long been one of the most frequently prescribed herbal formulas for treating dyspepsia. The current study is designed to evaluate the efficacy and safety of *Banha-sasim-tang *for FD patients and to examine whether there will be a significant correlation between cutaneous electrogastrography recordings and dyspeptic symptoms in FD patients, and between changes in gastric myoelectrical activity and improvement in dyspeptic symptoms during *Banha-sasim-tang *administration.

**Methods:**

This randomized, double-blind, placebo-controlled trial will be performed at two centers and will include a *Banha-sasim-tang *group and placebo group. Each group will consist of 50 FD patients. Six weeks of administration of *Banha-sasim-tang *or placebo will be conducted. During the subsequent 2 months, follow-up observations of primary and secondary outcomes will be performed. The primary outcomes are differences as measured on the gastrointestinal symptom scale, and the secondary outcomes are differences as measured on the visual analogue scale for dyspepsia and on the questionnaire for FD-related quality of life. All outcomes will be measured at baseline, at 2, 4, and 6 weeks of treatment, and at the 1 and 2 month follow-up. Cutaneous electrogastrography will be performed and assessed at baseline and at 6 weeks.

**Discussion:**

This trial will provide evidence of the safety and efficacy of *Banha-sasim-tang *for the treatment for FD. Furthermore, based on the assessment of the relationship between cutaneous electrogastrography recordings and dyspeptic symptoms in this trial, the possibility of clinical applications of cutaneous electrogastrography in the treatment of FD will be elucidated.

**Trial Registration:**

Current Controlled Trials (ISRCTN 51910678); Clinical Trials.gov Identifier: NCT00987805

## Background

Functional dyspepsia (FD) is characterized by chronic or relapsing dyspeptic symptoms in the absence of structural lesions that can be identified with clinically available tests [1,2]. In developed countries, 15-20% of the general population experiences dyspeptic symptoms at some point over the course of any given year [3]. An epidemiologic survey conducted in South Korea reported that 25% of the population suffers from FD [4].

Although the pathogenic causes of FD remain unclear, delayed gastric emptying has been found in up to 50% of FD patients [5]. Delayed gastric emptying may be attributed to gastric hypomotility and to uncoordinated antral duodenal contractions [6]. Normal gastric slow waves originating in the gastric pacemaker lead to normal frequency and peristaltic gastric contractions [5]. Abnormal gastric myoelectrical dysrhythmias has been observed in FD patients who have shown delayed gastric emptying [5]. Cutaneous electrogastrography (EGG) is a non-invasive diagnostic technique that detects gastric myoelectrical activity (GMA). Many researchers have used cutaneous EGG, which suggests that this technique may be useful in the evaluation of gastric motor function in FD patients [7]. However, the relationship between dyspeptic symptoms and cutaneous EGG recordings remains a controversial topic in FD.

Current treatments for FD target putative underlying mechanisms, including visceral hypersensitivity, impaired gastric emptying, and acid hypersensitivity [8]. The symptoms of FD are diverse, thus mechanism-focused therapies, such as acid secretion inhibitors, prokinetics, and *H. pylori *eradication, have been used with limited effects [8-10]. Therefore, many patients use alternative therapies, including herbal formulas, acupuncture treatments, and natural products, to treat FD [2,11-16].

*Banha-sasim-tang *(BST; *Hange-shashin-to *in Kampo Medicine; *Banxia-xiexin-tang *in Traditional Chinese Medicine) is one of the herbal formulas described in "Treatise on Cold Damage and Miscellaneous Diseases (*Shan-han-za-bing-lin*)" [17], the Chinese authoritative monographs. This formula is composed of seven herbs. In traditional Korean medicine, this formula has been applied for treating the symptom "gastric stuffiness" [17], which is similar to dyspepsia. Recently, several studies have elucidated the gastric function and related mechanisms of BST [18-20].

Moreover, BST can be obtained as an over-the-counter herbal formula in Korea or prescribed for dyspeptic symptoms by the Traditional Korean Medicine doctors. For that reason, reliable clinical evidence regarding BST as treatment for FD is needed. However, there are no relevant randomized controlled clinical trials regarding FD as far as we know.

The current study is designed to investigate the effect of BST on FD and related quality of life. We will also examine the relationship between the frequency or power variables in cutaneous EGG and dyspeptic symptoms of FD patients in this trial and determine whether the changes in GMA recorded by cutaneous EGG before and after the oral administration of BST can reflect the clinical efficacy of BST in the treatment of FD.

## Methods

### Objectives

The aims of this study are to:

(1) To determine whether BST can improve dyspeptic symptoms in patients with FD.

(2) To examine the relationship between dyspeptic symptoms and cutaneous EGG recordings and a possible biological evidence of BST's efficacy via cutaneous EGG recordings.

### Hypothesis

(1) Six weeks of oral administration of BST improves dyspeptic symptoms and quality of life in patients with FD.

(2) In patients with FD or FD subtypes according to the Rome III criteria, there will be a significant correlation between the degree of dyspeptic symptoms and cutaneous EGG recordings and 6 weeks of oral administration of BST can improve the abnormal frequency and power parameters on cutaneous EGG.

### Design

This study will be carried out as a randomized, placebo-controlled, double-blind, two-center trial at the Oriental Hospital at Kyung Hee University Medical Center and at the Oriental Hospital at the East-West Neo Medical Centre of Kyung Hee University in Seoul, Korea.

This clinical trial will consist of a 6-week oral administration of BST and a 2-month follow-up period. Before screening, all participants will go through a 7-day washout phase. During 6 weeks' administration of experimental drugs, patients will be prohibited from taking any kind of dyspepsia-relieving drugs. After randomization, 3 g TID of BST or placebos will be provided for 6 weeks. Outcomes will be measured at baseline, at 2 weeks, at 4 weeks and at 6 weeks after randomization. Outcomes will also be measured at 1 month and 2 months after completion of BST administration. During 2-month follow-up period, conventional treatments for dyspepsia will be permitted if the dyspeptic symptoms are exacerbated or recur. Any treatment received by the patient during the follow-up period will be reported by them or documented in their diary (Figure 1).

**Figure 1 F1:**
[figure not shown]
**Flow chart of the trial**.

This study will be performed in accordance with the standards of the International Committee on Harmonization on Good Clinical Practice and the revised version of the Declaration of Helsinki. The protocol of the trial has been approved by two ethics committees: the institutional review boards of both the Oriental Hospital at Kyung Hee University Medical Center and the Oriental Hospital at East West Neo Medical Center of Kyung Hee University. The permission numbers are KOMC IRB 2009-05 for the Oriental Hospital at Kyung Hee University Medical Centre and KHNMC-OH-IRB 2009-001 for the Oriental Hospital at East-West Neo Medical Centre of Kyung Hee University. Written informed consent will be obtained from all participants prior to enrollment, and patients will be given enough time to decide if they wish to participate before signing the consent form.

### Participants

#### Inclusion criteria

Patients 19-75 years old who complain of dyspepsia for the previous 3 months, and who have an onset of symptoms at least 6 months prior, meet the definition of the Rome III criteria for FD [21]. Patients with one or more of the following symptoms: postprandial fullness, early satiety, epigastric pain or burning, will be also considered as meeting the study definition of FD. Then, all the participants will undergo endogastroduodenoscopy (EGD) before enrollment and be examined by gastroenterologists to determine whether the EGD observations are related to the present dyspeptic symptoms. On the other hand, the *Helicobacter pylori *status of the patients and history of *H. pylori *eradication therapy will be assessed before enrollment by non-invasive tests (urea breath test) or the rapid urease test.

Patients who are diagnosed with FD can be categorized as having either 1) meal-induced dyspeptic symptoms (postprandial distress syndrome; PDS) or 2) epigastric pain syndrome (EPS) and, in this trial, all FD patients will be classified into one of the abovementioned subtypes (PDS and EPS) [21]. The dyspepsia severity of patients who meet the Rome III criteria will be assessed by a validated Gastrointestinal Symptom (GIS) scale, which measures the severity of 10 symptoms [22]. The presence of "moderate" as the degree of severity for at least three GIS scale symptoms will be a basic criterion for trial inclusion [2].

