### Statistical analysis

The primary hypothesis is that oral administration of BST is more effective than placebo for treating FD. We hope to prove this hypothesis by means of a 2-sided test yielding a 5% significance level. Because there is no relevant previous study using BST for calculating sample size, we referred to a similar herbal trial for FD treatment which used the GIS scale [1]. The formula for estimating the sample size is as follows:

The previous trial demonstrated 3.5 points of improvement (*μ*_*c *_- *μ*_*t *_= *Δ*) in the GIS scale over treatment with placebo during 4 weeks of herbal treatments [1]. The same study indicated a mean standard deviation (SD = *σ*) of 5.37. In our study, the ratio (*λ*) of experimental group to placebo group will be 1:1. With a power of 80% (1 - β) and significance level of 5% (α), assuming Δ = 3.5 and σ = 5.37, a sample size of *n_t _*= *n_c _*= 37 patients per treatment group will be required. (*n_t_*, number of BST group; *n_c_*, number of placebo group). Considering an assumed dropout rate of 25%, a total of 100 patients will be needed.

The analysis strategy in this study is as follows:

As a first step, the baseline characteristics of both groups, sex, age, duration of dyspeptic periods, and smoking, will be compared. As a second step, we will compare the efficacy of BST and placebo, as the change in GIS totals from the beginning (0 day) to the end (6 weeks) of the study period. As a third step, we will analyze the secondary variables (VAS and FD-QoL) in the same manner as we did the GIS scale. Finally, various parameters in the EGG measurement, such as frequency and power-related variables will be compared before and after treatment in both groups. Correlations between changes in GIS scale results and EGG parameter findings will also be analyzed.

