All analyses in this study will be based on the intention-to-treat principle. If data distribution is skewed owing to insufficient sample size, relevant transformation by a statistician prior to analysis will be made. The baseline characteristics will be compared by either *χ*^2^-test or the Student *t*-test. Primary and secondary outcomes will be presented as means and SDs, and analyzed by independent *t*-tests, Mann-Whitney tests, or Wilcoxon singed-rank tests. Correlations between the GIS scale and EGG parameters will be analyzed by Pearson's correlation coefficients or by Spearman's Rho. Adverse events will be calculated and compared using *χ*^2^-test or Fisher's exact test.

Statistical analyses will be conducted in a blind manner by an independent statistician and performed using SPSS 16.0 (SPSS inc., Chicago, Illinois, USA).

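### Every patient is put in exactly one of PDS or EPS, although the entry criteria admit patients with both kinds of symptom and no class or assignment rule is shown for them

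*Protocol article*

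**What the plan says.** Only the protocol article is at hand. Four of its statements bear on the point.

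- **Inclusion criteria, subtype definition.** Diagnosed patients "can be categorized as having either 1) meal-induced dyspeptic symptoms (postprandial distress syndrome; PDS) or 2) epigastric pain syndrome (EPS".
- **Inclusion criteria, subtype rule.** In this trial "all FD patients will be classified into one of the abovementioned subtypes (PDS and EPS". The rule covers everyone and offers two classes.
- **Inclusion criteria, entry symptoms.** "Patients with one or more of the following symptoms: postprandial fullness, early satiety, epigastric pain or burning" are counted as meeting the study definition of FD.
- **Hypothesis (2).** "In patients with FD or FD subtypes according to the Rome III criteria" a significant correlation is predicted between the degree of dyspeptic symptoms and the EGG recordings.

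The Statistical analysis section plans the correlations without naming subtypes: "Correlations between the GIS scale and EGG parameters will be analyzed by Pearson's correlation coefficients or by Spearman's Rho". The Exclusion criteria do not mention patients who have both meal-related and epigastric symptoms.

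**The concern.** The classification is exclusive and the entry rule is not. A patient with early satiety and epigastric burning is eligible, has symptoms of both kinds, and must still be given a single label. The text does not show which one.

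The label matters for one purpose. Hypothesis 2 is stated for the subtypes as well as for FD as a whole, so the label decides whose data enter a correlation reported for PDS or for EPS. If patients with both kinds of symptom sit inside a class named after one syndrome, that correlation does not describe patients with that syndrome alone. If only the single label is recorded, it may not be possible to separate these patients later.

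**Working it through.** The plan gives no figure for this point, so the check is mainly a comparison of its statements, with a count.

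**1. Can a patient have both kinds of symptom under the entry rule?**
The Inclusion criteria list four symptoms: two meal-related (fullness after meals, early satiety) and two epigastric (pain, burning). At least one is required.
- Non-empty combinations: 2^4 − 1 = 15.
- Meal-related only: 2^2 − 1 = 3.
- Epigastric only: 2^2 − 1 = 3.
- At least one of each kind: 3 × 3 = 9.

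So 9 of the 15 admissible patterns are mixed and 6 fall clearly on one side. This counts patterns; it is not a prevalence.

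**2. Does anything else remove or place the mixed patients?**
The Exclusion criteria do not remove them. The subtype rule has no third class, and the article shows no rule for choosing between the two.

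**3. How many patients could this concern?**
The document gives no overlap share. If it were 10%, 30% or 50% (assumptions), then 10, 30 or 50 of the 100 planned patients would be affected.

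**4. What depends on the label?**
- *Primary outcome:* change in the GIS total, BST against placebo. The label is not used.
- *Sample size:* n = 2(1.960 + 0.842)² × 5.37² / 3.5² ≈ 36.95, so 37 per group, as the plan states. Then 37 / (1 − 0.25) = 49.3, so 50 per group and 100 in total, also as stated. The label is not used.
- *Overall symptom-EGG correlation in FD:* the label is not used.
- *Symptom-EGG correlation within a subtype (Hypothesis 2):* the label decides membership.

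Only the last item is affected, and within it only through patients who have both kinds of symptom.

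**The case against.** The strongest reply is that an article condenses. The subtype definitions are cited to a source that is not shown, and the full protocol or case report form may contain an assignment rule, for example by predominant symptom. Having a symptom is also not the same as meeting a syndrome's criteria: the list of entry symptoms defines FD, not PDS or EPS. The Statistical analysis section names no subtype analysis, so the matter is exploratory at most.

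Much of this stands. What remains is that the article states a positive rule of one class per patient. A tie-break elsewhere would make assignment reproducible, but a patient with both kinds of symptom would still be counted under a single syndrome.

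Three stronger readings are tempting, and the document does not support them.

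- **Assignment is arbitrary or left to the site.** A reader might infer this from the missing rule. The text shows only that assignment is unspecified for these patients; it says nothing about who decides.
- **The severity criterion makes overlap likely.** The criterion requires moderate severity "for at least three GIS scale symptoms will be a basic criterion for trial inclusion", but the scale has ten items and several belong to neither subtype. Of C(10,3) = 120 three-item sets, C(9,2) − C(7,2) = 36 − 21 = 15 pair epigastric pain with fullness or early satiety. This again counts patterns, but it shows that the criterion can be met without both kinds of symptom.
- **A difference between subtypes shrinks toward zero by a known factor.** No comparison of PDS with EPS is planned, and any factor comes from its assumptions. Suppose pure-type correlations of 0.40 and 0, overlap patients at 0.20 and split evenly, and correlations that average linearly (not true in general). With 35 pure PDS, 35 pure EPS and 30 overlap patients, the two classes have (35×0.40 + 15×0.20)/50 = 0.34 and (15×0.20)/50 = 0.06, a difference of 0.28. With 60, 10 and 30, they have (60×0.40 + 15×0.20)/75 = 0.36 and (15×0.20)/25 = 0.12, a difference of 0.24. The overlap share is the same and the answer differs.

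**Conclusion.** The point holds in a limited form. The exclusive two-way classification does not fit the non-exclusive entry criteria, and the article shows neither an overlap class nor an assignment rule. Any within-subtype symptom-EGG correlation under Hypothesis 2 would include patients who also carry the other subtype's symptoms, if such patients are enrolled.

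Neither the size nor the direction of the effect can be stated, because the document gives no overlap share and no expected correlations. Patients with only one kind of symptom are not affected. A reader might infer that the trial's efficacy result is weakened; it is not, since the randomised comparison does not use the subtype. This is a minor point and a cheap improvement.

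**What to change.** Replace the single subtype label with two baseline items on the case report form: PDS criteria met (yes/no) and EPS criteria met (yes/no). Run the exploratory subtype correlations in three groups: PDS only, EPS only and both. Reword the Inclusion criteria to match. The two-way label can still be derived for patients who meet one set of criteria only. If no patient meets both, the third group is simply empty and nothing is lost.

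The cost is one form entry and some wording. The symptoms are already assessed at entry, so no procedure, eligibility rule or sample size changes.

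The drawback is smaller pure-subtype groups. As an illustration, take a two-sided 5% level and 80% power, which the plan sets for its primary comparison and which are assumed here for a correlation. The smallest detectable correlation is then about tanh[(1.960 + 0.842)/√(n − 3)]: 0.28 for n = 100, 0.39 for n = 50 and 0.54 for n = 25. The group sizes are assumptions. That loss is acceptable for an exploratory analysis, but the subtype results should be reported as estimates with intervals and labelled exploratory.

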#### Exclusion criteria

Patients who report the following conditions will be excluded:

History of peptic ulcer, gastroesophageal reflux disease (GERD), gastrointestinal surgery or mental disorders, marked current symptoms of irritable bowel disease, the presence of the alarm symptoms such as severe weight loss, black or tar stool, dysphagia, the presence of uncontrolled severe organ diseases including cancer, ingestion of aspirin or nonsteroidal anti-inflammatory drugs (NSAIDs), and women who are pregnant or lactating.

At the screening phase, patients who are using any antibiotic, proton-pump inhibitor, bismuth salt, prokinetic agents such as itopride, herbal formulas, or who are participating in any other clinical trial, will be excluded from this study.

### Recruitment

Recruitment will be done through hospitals and with newspaper advertisements. Patients who have severe dyspeptic symptoms are likely to receive conservative therapies. Thus, interested patients with severe symptoms of functional dyspepsia may be recruited through hospitals. However, patients with mild to moderate symptoms of functional dyspepsia seldom receive regular hospital treatment. Recruitment advertisements in newspapers can attract those patients with less severe symptoms.

### Randomization

Randomization will be controlled by an independent clinical research coordinator (CRC). First, the randomization form with the basic information of the participant who has passed the screening phase will be transmitted in facsimile to the independent statistician. The randomization number in the randomization form will be left blank before arrival to the statistician. The statistician will then decide the randomization number based on the allocation sequence which has been generated by a random number creation program in advance and the statistician will return the randomization form filled in with the established number (specific ID number) to the CRC. The ratio of randomization allocation to the sites will be 1:1. The CRC will inform the investigators of the specific ID number. This procedure will be guaranteed by the authorized contract research organization (CRO).

### Blinding

In this trial, investigators will not be in contact with the CRC, the clinical pharmacist, or the statistician. The CRC will be separated from all researchers, thus the researchers will not have any influence on enrollment or randomization. The statistician will receive the randomization form in facsimile, fill in the blank and return it in order, thus any contact with other researchers cannot be made. The blinding procedure will also be verified by the authorized CRO.

### Experimental drugs

#### Banha-sasim-tang (BST)

BST has long been used in traditional Korean medicine to treat gastrointestinal diseases. According to recent experimental researches, BST has been known to reduce inflammation in inflammatory bowel diseases and diarrhea, to regulate gastrointestinal functional in FD, and to protect against the side effects of chemotherapy in gastrointestinal cancers [18-20,23,24].

Although many experimental studies suggest that BST can be used to treat FD, there are no randomized studies of BST as a treatment for FD as far as we know.

BST used in this trial is a brown, bitter herbal extract granule (Bansasin granule^®^, Hanpoong Pharm & Food Co., Ltd., Jeonju, Korea) produced according to Korean Good Manufacturing Practice. Bansasin granule^® ^is permitted and regulated by the Korean Food & Drug Administration. Each 3 g Bansasin granule^® ^(water-extracted BST mixed with starch and lactose) is composed of seven herbs: *Pinelliae Tuber *(the rhizome of *Pinellia ternata *(Thunb.) Breit., family Araceae) 1.67 g, *Scutellariae Radix *(the root of *Scutellaria baicalensis *Georgi, family Labiatae) 1.00 g, *Ginseng Radix *(the root of *Panax ginseng *C.A. Meyer, family Araliaceae) 1.00 g, *Glycyrrhizae Radix *(the root of *Glycyrrhiza uralensis *Fisch., family Leguminosae) 1.00 g, *Zizyphi Fructus *(the fruit of *Zizyphus jujuba *Mill. var. inermis Rehder, family Rhamnaceae) 1.00 g, *Zingiberis Rhizoma *(the rhizome of *Zingiberis officinale *Roscoe, family Zingiberaceae) 0.83 g, and *Coptidis Rhizoma *(the rhizome of *Coptis chinensis *Franch., family Ranunculceae) 0.33 g. As standard chemical components in each 3 g Bansasin granule^®^, 11.6 mg of berberin, 25.0 mg of glycyrrhzin acid and 100.0 mg of baicalin are included. Voucher specimens will be retained at the research laboratory of Hanpoong Pharm & Food Company. Regular dosage is 3 g TID for adults while dyspeptic symptoms, nausea, vomiting, diarrhea, abdominal pain, and anorexia continue.

